In humans, there is a growing body of evidence that gabapentin may have a positive effect on the amount of motor recovery as measured by the Total Motor Score (TMS) of the International Standards for Neurological Classification of SCI (ISNCSCI). This is based on retrospective analysis of the prospective European Multicenter SCI (EMSCI) observational study database. It was initially discovered, while performing an analysis related to pain, that individuals in the database who had been administered anticonvulsant medication within the 1st month post-injury gained an average of 7.3 additional TMS points at 1 year when compared to individuals who had not been administered anticonvulsant medication within the 1st month post-SCI (16). That cohort included individuals with tetraplegia and paraplegia as well as all levels of severity. A larger analysis confirmed the gain in motor recovery when anticonvulsants were started in the 1st month after injury (average of 6.3 additional TMS points at 1 year compared to those that were not administered anticonvulsants) and identified that the most frequently administered anticonvulsants were gabapentinoids (17). A gain of an average of 9 motor points is roughly equivalent to an improvement of one spinal segment, which can translate to a significant functional impact (as measured by the Spinal Cord Independence Measure) when the gain is in the cervical or lumbosacral regions (18). Good functional assessments of the thoracic segments are still lacking. An analysis of the Sygen database, a large (*N* = 797), well-designed clinical trial conducted primarily before gabapentinoids came to the market, revealed that non-gabapentinoid anticonvulsants given within 1-month post-SCI had no effect on total motor scores (19). Most recently, analysis of the EMSCI database enabled the longitudinal modeling of drug-by-time effect sizes on TMS point recovery with the largest effect size being when gabapentiniods were administered within the first 5 days following SCI (20). Interpretation of this effect size must be taken with caution, however, as it is based on a small number of cases (*n* = 14) and with no information regarding dose. To date, there have been no prospective studies evaluating early administration of gabapentin in humans with SCI.

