#### Secondary data analysis

Additionally, we will report the population demographics, adverse events, medications, outcome measures as well as pain characteristics and transitions. To do so we will calculate descriptive statistics for each outcome (e.g., frequency counts, percentages, means, medians, standard deviations, interquartile ranges, confidence intervals). We will report overall results within each cohort (placebo, 600, 1,800 mg gabapentin) as well as differences across cohorts. We will not test for statistical significance of efficacy because that is not the intent of this study.

In addition to using the descriptive statistics, we will perform a sensitivity analysis to inform a future efficacy trial. The literature suggests using the feasibility study's upper limit of the 80% confidence interval for the standard deviation when calculating the sample size needed for the future efficacy trial (52). We will analyze the blinded ISNCSCI total motor score results with confidence intervals at 75, 80, 85, 90, and 95% to get a preliminary, cautious view of efficacy/effect (22). This thorough sensitivity analysis will inform a sample size calculation for a future trial. Calculating the eligibility rate and the retention rate from this trial will also be helpful in estimating the duration of a future efficacy trial (22).

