### Limitations

We recognize that there are some limitations to this study protocol. One is that the placebo and gabapentin capsules are not identical. Participants could search online without the study team knowing and identify what treatment they are on based on the size, shape, color, and markings on capsules. By unblinding themselves this could create bias in the results. Also, the placebo and gabapentin capsules may taste different leading participants to identify which treatment they are on if they end up needing gabapentin for pain management after the 90-day treatment period. This could also create bias in the results.

The broad inclusion of all injury levels and severities and randomization scheme of grouping AIS A–B and AIS C–D is a limitation with regard to analyzing trends of neurologic recovery. As we are testing the feasibility of restricting/manipulating the use of gabapentin it is important that we understand the impact of that restriction for all injury levels and severities (e.g. ability to consent within the enrollment time window, potential swallowing difficulties) to be able to inform future trial enrollment criteria and randomization schema. Regarding the potential safety of gabapentin, it has been used broadly and at much higher clinical doses in all levels and severities of SCI so there is no strong rational to restrict inclusion based on injury level or severity. However, the heterogeneity of neurorecovery across injury levels and different AIS grades will have an impact on interpretability of efficacy results despite them intended to only be exploratory. A more appropriate randomization scheme for future trials may be to group AIS A by itself, AIS B–C together, and AIS D by itself.

Additionally, it is possible that even if all of the quantitative benchmarks of success are met regarding feasibility, protocol modification may be necessary to address heterogeneity of neurorecovery in a properly powered efficacy trial. We will have a strong understanding, however, of the ability to restrict the dosage of gabapentin and use a placebo for such a trial.

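### The total motor score analysis that will inform the efficacy trial's sample size makes no stated use of the Baseline score; a baseline-adjusted analysis would be more precise at almost no cost

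*Protocol article*

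**What the plan says.** Only the protocol article is at hand. Its Secondary data analysis section describes the calculation in four parts.

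- Reporting unit: "We will report overall results within each cohort (placebo, 600, 1,800 mg gabapentin) as well as differences across cohorts". The tools listed are descriptive: counts, means, medians, SDs, confidence intervals.
- Testing: "We will not test for statistical significance of efficacy because that is not the intent of this study".
- Motor score: "We will analyze the blinded ISNCSCI total motor score results with confidence intervals at 75, 80, 85, 90, and 95" per cent, for a cautious first look at effect.
- Use: "This thorough sensitivity analysis will inform a sample size calculation for a future trial". For the SD, the article reports a recommendation from the literature to take the "upper limit of the 80% confidence interval for the standard deviation when calculating the sample size needed for the future efficacy trial".

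The section does not say whether the motor score is taken as the score at a visit, as change from Baseline, or as a residual from a model. It names no covariate and no visit.

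Other sections supply the context. Table 2 and Exploratory efficacy assessments provide a blinded full ISNCSCI at Baseline, Interim, End of Treatment and End of Study. Eligibility criteria admit every injury level and AIS grades A to D. Sample size and Table 1 give 14 per arm, stratified only as AIS A–B and C–D. Assessments places Baseline at 7 days ±2 after injury, after study medication has begun.

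**The concern.** Participants will start from very different motor scores, and this will carry through to later scores to a degree that the correlation between the two measures. Stratifying on AIS in two groups does not balance injury level. Limitations itself acknowledges "The broad inclusion of all injury levels and severities and randomization scheme" as a difficulty for reading neurologic recovery, but offers no analytic remedy for this trial's own data.

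If the description is followed as it stands, two things follow. First, with 14 per arm, an arm difference in a later score includes whatever difference in starting score chance has produced. Second, the SD handed to the next trial's sample size includes variance that a known covariate would explain. The efficacy trial could then look larger than a baseline-adjusted design needs, and the pilot's intervals would be wider than its data allow.

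**Working it through.** **The plan's own figure.** 3 arms × (7 + 7) = 42, which reproduces the stated target. It rests on a rule of thumb, so there is no power calculation to check.

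**Inputs.** From the documents: 14 per arm; 80% interval; illustrative effects of 6.3 and 7.3 points (Introduction, retrospective cohorts; not design inputs). Assumed, because the documents give none: raw SD 20 (also 25 and 30), rho between Baseline and later score 0.3 to 0.8, equal SDs at both visits, and two-sided 5% significance with 80% power for the future two-arm trial.

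**Formulas.**

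- Residual SD after ANCOVA on Baseline = SD × √(1 − rho²).
- SD of change from Baseline = SD × √(2(1 − rho)).
- n per arm = 2 × (1.96 + 0.8416)² × SD² / effect².
- 80% half-width, 14 v 14 = t(0.90; 26 df) × SD × √(2/14) = 0.497 × SD.

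**Unadjusted, SD 20, effect 6.3.** n = 2 × 7.849 × 400 / 39.69 = 158.2, so 159 per arm. The half-width is 0.497 × 20 = 9.9 points.

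**Adjusted, same SD and effect.**

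| rho | ANCOVA variance factor | n per arm, ANCOVA | Change-score variance factor | n per arm, change score | 80% half-width, ANCOVA |
|---|---|---|---|---|---|
| 0.3 | 0.91 | 144 | 1.40 | 222 | 9.5 |
| 0.5 | 0.75 | 119 | 1.00 | 159 | 8.6 |
| 0.7 | 0.51 | 81 | 0.60 | 95 | 7.1 |
| 0.8 | 0.36 | 57 | 0.40 | 64 | 6.0 |

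The half-widths ignore the few degrees of freedom spent and any gain from adding the AIS stratum. The factors do not depend on the SD. At SD 25 and 30 the unadjusted n is 248 and 356, and at rho 0.7 it becomes 127 and 182.

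**Upper 80% limit of the SD.** The multiplier is √(df / χ²(0.10; df)). Pooled over three arms (df 42 − 3 = 39) it is 1.176. With Baseline and stratum in the model, df is 37, which lies between the values 1.185 (df 36) and 1.176 (df 39). The step therefore inflates adjusted and unadjusted sample sizes almost equally (1.176² = 1.38) and leaves the ratio between them in place.

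**Chance imbalance.** The standard error of the arm difference in Baseline score is SD × √(2/14) = 0.378 × SD. That is 5.7, 7.6 or 9.4 points at Baseline SD 15, 20 or 25, before any reduction from AIS stratification. An unadjusted later difference carries rho times the imbalance. At SD 20, a one-standard-error imbalance of 7.56 points contributes 3.8, 5.3 or 6.0 points at rho 0.5, 0.7 or 0.8. The cited effects are 6.3 and 7.3.

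**The case against.** The strongest reply is that silence is not a choice. The section never says raw or unadjusted, the word used for the motor score results could cover change from Baseline, and the article elsewhere presents the ISNCSCI as a measure of change. This is a condensed article about an exploratory outcome, and model and covariates are often left to fuller documents. That stands against calling this an error. It does not remove the point: the section does commit to a sizing use, and the score, change and residual SDs lead to different trial sizes.

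Four stronger readings are tempting, and the documents do not support them.

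- A reader might infer that an SD of the score is on the wrong scale for effects expressed as gains. Under randomisation the expected arm difference is the same for score and gain. The unadjusted interval is valid, only wider.
- A reader might use "A gain of an average of 9 motor points is roughly equivalent to an improvement of one spinal segment" to convert spread in injury level into score SD. That sentence equates a recovery gain with a segment. It is not a conversion for differences between people.
- A reader might infer that level-related variance is unrelated to recovery. Limitations says recovery itself varies by level and grade, so Baseline adjustment will not remove all of it.
- A reader might infer a firm commitment to an unadjusted SD as the sizing input. The text reports a suggestion and says the analysis will inform the calculation.

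Three further replies also stand. Feasibility is the primary endpoint and is untouched. Any excess in sample size would be on the cautious side. Baseline comes after the first dose, so it is not a clean pre-treatment covariate.

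**Conclusion.** The point holds as an efficiency improvement, not as a demonstrated mistake. As described, the motor score analysis makes no stated use of a Baseline measurement that the trial already collects, in a population where starting scores will vary widely and 14 per arm cannot be relied on to balance them. The direction is certain for any non-zero correlation, apart from the trivial degrees of freedom spent. The size cannot be established from the documents. Under assumed rho of 0.5 to 0.8, the future sample size would be 0.75 to 0.36 of the unadjusted one, while a plain change score would gain nothing at 0.5 and lose below it. The saving applies only if the efficacy trial is itself analysed with baseline adjustment; otherwise the unadjusted SD is the right input. The change is worth making before analysis, with no bearing on the feasibility conclusions.

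**What to change.** In Secondary data analysis, state that total motor score at End of Treatment and at End of Study is analysed by ANCOVA with arm, Baseline total motor score and AIS stratum (A–B, C–D). Then:

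- take the arm-difference intervals at all five levels from that model;
- take its residual SD, with the upper 80% limit, as the input for sizing an efficacy trial that will also adjust for Baseline;
- report the observed baseline-outcome correlation;
- show the unadjusted interval and SD alongside.

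The cost is two or three sentences and two degrees of freedom (39 to 37), with no new data. The one drawback is that Baseline follows the first dose, so any very early drug effect on it would be adjusted away. The unadjusted results shown alongside let a reader judge this.

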## Discussion

Because gabapentin is already FDA approved, is available generically, and has a long history of use in SCI, it is a prime candidate for drug repurposing. The risk to benefit ratio is attractive as well. Gabapentin has been used clinically in tens of thousands if not hundreds of thousands (or more worldwide) of individuals living with SCI and the risk profile is well known and relatively well tolerated. Gabapentin has a much lower risk profile than the only other medication previously used in the acute setting to improve neurologic outcomes in SCI: high-dose methylprednisolone (53). The unknown risk relates to the fact that gabapentin is being administered slightly earlier than usual for the clinical management of neuropathic pain (starting 5 days after injury as opposed to a few weeks or months after injury). Although, gabapentin is increasingly used in the post-operative period after acute trauma for pain management.

The preclinical and clinical evidence of benefit is strong enough to warrant moving forward to the next step in translation, which is this trial. Additionally, acute interventions available for traumatic SCI are severely lacking as only early surgical decompression and targeted spinal cord perfusion pressure have demonstrated likely benefits. There is the generally accepted belief in the field that significant clinically meaningful benefit will only come from the cumulative effective of multiple interventions with each contributing a marginal neurologic benefit (54); gabapentin could be one of the multiple interventions.

### Rationale for dose

Extrapolation of the human equivalent dose (HED) from an animal dose involves allometric scaling, which takes into account interspecies differences in anatomy and physiology and scales based on body surface area and body weight (55). Table 5 shows the HED calculated for the animal studies described in the introduction. The HED ranging from 8.1 to 16.2 mg/kg had positive neurologic effects in animals; the HED of 64.8 mg/kg did not have a neurologic effect in animals. In the USA, gabapentin is commonly available in 100, 300, and 400 mg capsules. Dosages in the retrospective analyses in humans described in the introduction were not defined, but likely ranged from 300 to 3,600 mg/day. The generally effective clinical dose for neuropathic pain with minimal side effects is approximately 1,800 mg/day. Based on all this information, it was decided to explore a low (600 mg/day) and medium (1,800 mg/day) dose of gabapentin in comparison to placebo.

**Table 5 T5:** Animal to human dose conversion.

**References**	**Species**	**Dose used and HED**	**Daily dose for 80 kg human**
Kitzman et al. (12)	Rats	50mg/kg; HED = 8.1 mg/kg	648 mg
Rabchevsky et al. (13)	Rats	50mg/kg; HED = 8.1 mg/kg	648 mg
Rabchevsky et al. (14)	Rats	50mg/kg; HED = 8.1 mg/kg	648 mg
Eldahan et al. (56)	Rats	400 mg/kg; HED = 64.8 mg/kg	5,184 mg
Sun et al. (15)	Mice	92–138 mg/kg; HED = 7.4–11.2 mg/kg	592–896 mg
Brennan et al. (4)	Mice	200 mg/kg; HED = 16.2 mg/kg	1,296 mg

### Rationale for start time

In the animal studies described above, gabapentin was started immediately after SCI or within the first day. The human literature suggests that the largest effects may be achieved when gabapentin is started within 0–5 days of injury. Therefore, the target enrollment window is as soon as possible following admission to the hospital and extending through 5 days (120 h) post-injury.

### Rationale for duration of treatment

From the animal literature, the duration of dosing ranged from 14 to 131 days post-SCI, with the average across studies being 52 days (4, 14, 15, 56). In humans, spinal shock typically ends, and early hyperreflexia emerges by 1-month post injury, with late hyperreflexia emerging between 1 and 12 months' post-injury (57). With this combined information, a 90-day treatment duration was chosen for this first prospective study.

### Input from stakeholders

Input on the topic and design of this trial was obtained from our Community Advisory Board (CAB), composed of individuals living with SCI, in an iterative manner. In the initial idea-generation phase of this trial, exceedingly helpful input was obtained from the CAB. During a preliminary meeting, they indicated their approval with use of low dose gabapentin (there was concern about side effects of high doses used in chronic pain management) and with alternative pain management options. Given a discussion about participants receiving gabapentin unnecessarily (e.g., for research), the CAB sought to ensure that people would be weaned off the study drug, which was built into the design at the end of the 90-day treatment period. To address their concern that autonomy be maintained, it was decided to include only those personally able to give informed consent during the enrollment window. The CAB did not question the inclusion of either a placebo group or dissolving the drug in water, should anyone be unable to swallow pills temporarily. Their input was incorporated into the final design of this study, which was then communicated back to the CAB and their approval was obtained.

We also sought input from MetroHealth System clinical sub-specialists that are key contributors in the clinical care for SCI and this project: Trauma, Neurosurgery, Pain Management, Nephrology, and PM&R. They all provided input to different aspects of the trial and several agreed to serve in an advisory role. Finally, we sought input from scientists external to the study team. One has published the retrospective analyses of the effect of gabapentin on neurorecovery in humans ([name]) and the other has published several prospective animal studies demonstrating the effect of gabapentin on the autonomic system ([name]). Both individuals agreed to serve in an advisory role throughout the trial.

### Limitations

We recognize that there are some limitations to this study protocol. One is that the placebo and gabapentin capsules are not identical. Participants could search online without the study team knowing and identify what treatment they are on based on the size, shape, color, and markings on capsules. By unblinding themselves this could create bias in the results. Also, the placebo and gabapentin capsules may taste different leading participants to identify which treatment they are on if they end up needing gabapentin for pain management after the 90-day treatment period. This could also create bias in the results.

The broad inclusion of all injury levels and severities and randomization scheme of grouping AIS A–B and AIS C–D is a limitation with regard to analyzing trends of neurologic recovery. As we are testing the feasibility of restricting/manipulating the use of gabapentin it is important that we understand the impact of that restriction for all injury levels and severities (e.g. ability to consent within the enrollment time window, potential swallowing difficulties) to be able to inform future trial enrollment criteria and randomization schema. Regarding the potential safety of gabapentin, it has been used broadly and at much higher clinical doses in all levels and severities of SCI so there is no strong rational to restrict inclusion based on injury level or severity. However, the heterogeneity of neurorecovery across injury levels and different AIS grades will have an impact on interpretability of efficacy results despite them intended to only be exploratory. A more appropriate randomization scheme for future trials may be to group AIS A by itself, AIS B–C together, and AIS D by itself.

Additionally, it is possible that even if all of the quantitative benchmarks of success are met regarding feasibility, protocol modification may be necessary to address heterogeneity of neurorecovery in a properly powered efficacy trial. We will have a strong understanding, however, of the ability to restrict the dosage of gabapentin and use a placebo for such a trial.

## Ethics and dissemination

This trial has received ethical approval from the MetroHealth System Institutional Review Board (IRB21-00609). No changes to the protocol will be implemented prior to obtaining ethical approval.

Informed consent will be obtained by the investigators and clinical research staff in consultation with the participant. As this study has an enrollment time window cut off of 120 h post-injury, the study team will identify potential participants as quickly as possible after they are admitted to the hospital following their injury. Most individuals who sustain a traumatic SCI are admitted to this site within less than 24 h of injury onset. The goal of identifying potential participants as soon as possible after admission is to allow as much time as possible for the consent process and to include family members when requested by potential participants.

Results will be disseminated through presentation at peer-reviewed academic meetings and by publication in peer-reviewed medical journals. Publications will be shared with the Model Systems Knowledge Translation Center and the National Rehabilitation Information Center. Summaries of different results will be shared with the community living with SCI as well as clinical providers as appropriate.

## Data sharing

A deidentified dataset will be shared after the end of the award. The data will be processed into a usable format and then a copy of the de-identified dataset will be transferred to the Interuniversity Consortium for Political and Social Research (ICPSR) for data sharing and long-term preservation. The data will be released to the public no later than 24 months after the award end date. The dataset will have a digital object identifier, provided by ICPSR, for future reference and citation.

